## Abstract

**Introduction:**

Type 2 diabetes is associated with excess hospital admissions and increased mortality. Structured diabetes self‐management education (DSME) is recommended internationally and is associated with improved self‐management skills, well‐being and minor improvements in glycated haemoglobin (HBA1c), but does it reduce hospital admissions or prevent premature mortality? Our aim is to examine the relationship between DSME attendance, hospitalisations, mortality and 3‐point major adverse cardiovascular events (MACE) in people with type 2 diabetes to inform future healthcare policy and diabetes care.

**Methods and Analysis:**

This protocol details a 10‐year retrospective open cohort study of patients aged over 18 years old who have a clinical diagnosis of type 2 diabetes and were registered to an English GP practice from 29 March 2011 to 29 March 2021 and have attended DSME. Patients in the '*ever*' cohort will be matched at baseline for age, sex, age at diagnosis and diabetes duration, to those who have '*never*' attended DSME. Data will be identified via the UK Clinical Practice Research Datalink and linked to Hospital Episode Statistics Admitted Patient Care data, Office for National Statistics death registrations and patient Index of Multiple Deprivation deciles. Patients will be followed‐up through serial cross‐sections. Multiple imputation will be considered to manage covariates where data are >12‐months from baseline or are not expected to be missing at random. Cox proportional hazard regression and time to event modelling adjusted a priori for cofounding during multivariate analysis will be used.

**Ethics and Dissemination:**

This study was approved by CPRD (24_003744). Study findings will be disseminated through peer‐reviewed publications and international conferences.

## INTRODUCTION

1

Diabetes is a complex condition leading to disability and premature mortality with 7000 excess deaths in the United Kingdom in 2022.^1^ The International Diabetes Federation estimates 537 million people are living with diabetes globally^2^ of whom approximately 4.3 million reside in the United Kingdom.^3^ Over 90% have type 2 diabetes, with an increased prevalence in areas with high deprivation, poor healthcare access, poorer housing, reduced finances and lower educational attainment.^3^

Diabetes self‐management education (DSME), which includes support for healthy food and lifestyle choices, is fundamental to achieving good glycaemic control and is recommended internationally to help prevent diabetes‐related micro‐ and macrovascular complications.^4^, ^5^ Indeed, early delivery of DSME with timely pharmacotherapy may be particularly beneficial through the so‐called *legacy effect*.^6^, ^7^

Despite the National Institute for Health and Care Excellence (NICE),^5^ American Diabetes Association (ADA) and the European Association for the Study of Diabetes (EASD) stating that DSME is the foundation for successful diabetes management and prevention of metabolic comorbidities,^4^ the UK National Diabetes Audit suggests of 71% of people with type 2 diabetes offered DSME, only 7% attend.^8^

Approximately 20% of all UK hospital beds are currently occupied by people with diabetes and the number is expected to rise to 25% by 2030,^9^ most (92%) are admitted for other conditions and illnesses.^10^, ^11^

Of studies examining the impact of DSME on hospital admissions (*n* = 15), wide variability exists in the completeness of outcome data, confounding variables and design details making direct comparisons challenging. Four studies found DSME significantly impacted hospitalisations.^12^, ^13^, ^14^, ^15^ Time to first hospitalisation was significantly increased (*p* = 0.002) in a cohort of 376 US patients with type 2 diabetes over a 2‐year follow‐up, however, groups were not matched at baseline.^12^ A large cohort study in Hong Kong concluded that all‐cause admission rates significantly reduced following DSME in the 2‐year follow‐up, including those who only attended one session, with substantial delays to first admission and reduced recurrent admissions after DSME.^13^ In Serbian patients with type 2 diabetes, rates of admission due to metabolic conditions significantly reduced (*p* = 0.001) in the 6 months after DSME^14^ but longer term follow‐up was not reported. In Austria, although DSME did not impact number of admissions, it significantly reduced length of hospital stay (*p* = 0.04)^15^ but prevalence of type 2 diabetes in Austria is lower than other developed countries and all participants were recruited from one large teaching hospital potentially reducing its generalisability.

In studies examining the impact of DSME on mortality, most (*n* = 28) cite mortality as a reason for drop‐out rather than examining mortality as a primary outcome measure,^13^, ^16^, ^17^, ^18^ and only two studies report significant improvements following DSME.^13^, ^16^ In a study from Hong Kong, attending one or more DSME sessions was associated with lower all‐cause mortality (HR:0.59, CI 95% 0.632–0.968, *p* = 0.024); however, differences existed between study groups,^13^ with similar findings described in a UK randomised control trial, where mortality in participants requiring ambulance transfer for severe hypoglycaemia was 33.3% in those that had attended DSME compared with 51.2% in those receiving standard care without DSME (HR 0.65, *p* = 0.025).^16^ DSME workshops for an elderly Argentinian type 2 cohort resulted in an 33% lower 6‐year crude mortality rate, but significance was lost in multivariate analysis showing only a weak (18%) association between DSME attendance and reduced mortality (HR 0.82; 95%CI: 0.61–1.08) but socio‐economic data was not reported as a confounder, and those in the non‐attendance group had an increased stroke prevalence, higher diastolic blood pressure and LDL‐C which could explain the increased mortality rate.^17^ This weak association between DSME attendance and mortality was also reported in an earlier study which simulated the long‐term cost‐effectiveness of DSME interventions over 20 years, however, results obtained in this simulated RCT may not be representative of diabetes care delivered outside of this type of clinical trial.^18^

In short, existing studies provide evidence that DSME improves well‐being, self‐management skills and short‐term blood sugar control (HbA1c), but crucially evidence of an impact of DSME on hospital admissions and premature mortality is limited and conflicting and has not been assessed in a real world setting on this scale.

## AIMS AND OBJECTIVES

2

The aim of this large retrospective cohort study is to examine the impact of DSME attendance on all‐cause and cause‐specific hospital admissions and mortality in people with type 2 diabetes, utilising linked large UK national datasets to test the hypotheses that DSME attendance impacts all‐cause hospital admissions and mortality.

The specific objectives are to:To describe the epidemiology of patients living with type 2 diabetes who have attended DSME by age, sex, ethnicity, deprivation levels (IMD), HbA1c and baseline Charlson Comorbidity Index in a representative sample of a large cohort of adults who were registered with an English GP between 2011 and 2021.To examine the association between ever or never having attended DSME on all‐cause and cause‐specific hospital admissions, in adults with type 2 diabetes.To examine the association between ever or never having attended DSME on all‐cause and cause‐specific mortality, including but not confined to in‐hospital mortality.To examine the association between ever or never having attended DSME on major adverse cardiovascular events (3P‐MACE); CV death, non‐fatal myocardial infarction (MI) and non‐fatal stroke, in adults with type 2 diabetes.

## METHODS AND ANALYSIS

3

This study will be conducted, analysed and reported in line with the STrengthening the Reporting of OBservational studies in Epidemiology (STROBE) checklist for cohort studies.^19^, ^20^

### Study design

3.1

This 10‐year retrospective open cohort study^19^ will include adults over the age of 18 years^†^, 12 months from the first use of a clinically recorded diagnosis of type 2 diabetes or type 2 diabetes‐related encounter registered to an English GP practice between 29 March 2011 and 29 March 2021^‡^. Patients will be identified from the CPRD database using READ codes to run analyses of the agreed set of exposures and outcomes.

^†^Patients who turn 18 during the study period will be included from the point of turning 18.

‡At the time of CPRD approval for this protocol data linkage to Hospital Episode Statistics (HES) Admitted Patient Care (APC) data were restricted up to and including 29 March 2021.

### Sample

3.2

Patients will be stratified into two groups dependent on their exposure to DSME. The primary cohort is those who have a READ code confirming they have ‘*ever’* received DSME (*n* = 21 298) (Table 1 lists the Med Code IDs for exposure to DSME). Guidelines recommend DSME for all patients newly diagnosed with type 2 diabetes.^5^ To allow sufficient time for exposure to DSME and to account for immortal time bias^21^ any hospitalisations or deaths within the first 12 months of diabetes diagnosis will be excluded in both ever and never DSME groups as it is likely that there will be a period during the 12 months in which patients have not had the opportunity to be exposed to the intervention.

**TABLE 1 dom16257-tbl-0001:** DSME Med Code IDs.

Med Code ID	Term
2 533 102 013	Attended diabetes structured education programme
5.32331E+14	Diabetes structured education programme completed
5.46001E+14	Attended XPERT diabetes structured education programme
5.46221E+14	DESMOND diabetes structured education programme completed
5.46291E+14	XPERT diabetes structured education programme completed
6.84397E+15	Attended diabetes structured education programme
8.09822E+15	Attended expert patient education versus routine treatment diabetes structured education programme
8.09824E+15	Attended XPERT (expert patient education versus routine treatment) diabetes structured education programme
8.09835E+15	Expert patient education versus routine treatment diabetes structured education programme completed
8.09837E+15	XPERT (expert patient education versus routine treatment) diabetes structured education programme completed
1.21156E+16	Remote diabetes structured education and support programme commenced
1.21156E+16	Remote diabetes structured education and support programme completed

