### Data selection

3.3

To minimise the impact of incorrect information or flawed subject selection the ‘*ever’* cohort will be matched at baseline to patients who have ‘*never’* received DSME (*n* = 584 312). Age,^22^, ^23^ age at diagnosis and diabetes duration^22^, ^24^, ^25^, ^26^ are the most important predictors of one‐year mortality in type 2 diabetes.^27^ Every decade of earlier diabetes diagnosis is associated with 3–4 years of lower life expectancy.^24^

Cohort analysis, systematic review and meta‐analysis have considered the association between diabetes and sex, demonstrating that women generally have a higher risk of coronary heart disease and all‐cause mortality (58%) compared to men and a 13%–17% greater risk of all‐cause mortality.^28^, ^29^ Moreover, the additional likelihood of developing cancer and the higher risk of premature mortality from having diabetes is more pronounced in women.^30^

Patients will therefore be matched at baseline for age ± 5 years, age at diagnosis ±5 years, diabetes duration ±1 year and sex who are present in the dataset from the same start year or earlier.

This study will adopt an intention‐to‐treat analysis, with patients contributing only to the original exposure group in which they have been assigned, irrespective of when they receive DSME. Baseline for the ‘ever’ group and their matched controls will be the date of DSME intervention. Patients will remain exposed until they are censored by death, leave the GP practice, leave a GP practice which contributes to CPRD data or end of the study period (29 March 2021).

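### Follow-up runs from the DSME date but the 12-month event exclusion runs from diagnosis, so the entry rules conflict for first-year attenders and can leave matched partners with unequal event time

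*Protocol article*

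**What the plan says.** Three sections of the protocol article bear on when a patient starts to contribute.

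- Section 3.1 (Study design) includes adults 12 months "from the first use of a clinically recorded diagnosis of type" 2 diabetes. This can be read as entry at diagnosis plus 12 months.
- Section 3.2 (Sample) states that hospitalisations and deaths in the first 12 months "of diabetes diagnosis will be excluded in both ever and never DSME groups". The reason given is "To allow sufficient time for exposure to DSME and to account for immortal time bias". The same section notes that guidelines recommend DSME for all newly diagnosed patients.
- Section 3.3 (Data selection) says that baseline for the ever "group and their matched controls will be the date of DSME intervention". Controls are matched on age, age at diagnosis, "diabetes duration ±1 year and sex who are present in the dataset from the same start year or earlier".

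Section 3.6 (Statistical methods) then compares crude proportions hospitalised or dead by chi-squared test, models admission counts by mixed Poisson or negative binomial regression, and models time to first admission and death by Cox regression.

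The article does not say whether the person-time of the excluded 12 months is removed along with the events, or whether a patient who dies in that period is dropped.

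**The concern.** The exclusion window is measured from diagnosis and follow-up is measured from DSME. For a patient educated in the first year, the first part of follow-up lies inside the window. Sections 3.1, 3.2 and 3.3 then cannot all be applied as written: either the patient enters at the DSME date, or at diagnosis plus 12 months.

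The tolerance on diabetes duration (±1 year) is as wide as the window (12 months), so an attender inside the window can be paired with a control already outside it, or the reverse. Duration cannot fall below zero, so controls of very early attenders tend to have longer duration than their partners. The imbalance is then systematic and does not average out.

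At stake is whether the ever/never contrast equals 1 when DSME has no effect. Time zero enters every outcome comparison in the study.

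**Working it through.** **Inputs from the protocol.** Baseline at DSME date and duration match ±1 year (section 3.3); 12-month exclusion from diagnosis (section 3.2). The protocol gives no figure of its own for the effect of this rule, so there is none to reproduce.

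**Assumptions, because the protocol gives no values.** No true effect of DSME; constant event rate; control duration uniform over the permitted range, floored at 0; follow-up F of 2 or 5 years from baseline; several distributions of DSME timing. First-event and proportion results also assume 0.2 events per year.

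**One permitted pair.** The attender has DSME 2 months after diagnosis and the control has a duration of 14 months. The attender loses 12 − 2 = 10 months of events and the control none. If only events are deleted, the pair's null rate ratio is (2 − 10/12)/2 = 0.58 at 2 years and (5 − 10/12)/5 = 0.83 at 5 years.

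**Event time lost, in years, with DSME at d years after diagnosis.**

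- Attender: max(0, 1 − d).
- Control, d below 1: duration is uniform on 0 to 1 + d, so the mean loss is 0.5/(1 + d).
- Control, d from 1 to 2: duration is uniform on d − 1 to d + 1, so the mean loss is (2 − d)²/4.
- d of 2 or more: neither partner is in the window, and both lose 0.

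**Events removed, person-time kept.** Null rate ratio = (F − mean attender loss)/(F − mean control loss).

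- DSME spread evenly over the first year: attender 0.5; control 0.5 × ln 2 = 0.347 (6.0 and 4.2 months). Ratio 1.5/1.653 = 0.91 at 2 years; 4.5/4.653 = 0.97 at 5 years.
- DSME spread evenly over 1 to 2 years: attender 0; control 1/12 = 0.083. Ratio 2/1.917 = 1.04; 5/4.917 = 1.02.

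Simulation of one million pairs per scenario gave the same values and added the first-event rate:

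| DSME timing after diagnosis | All events, 2 y | All events, 5 y | First event, 2 y | First event, 5 y |
|---|---|---|---|---|
| Uniform 0–12 months | 0.91 | 0.97 | 0.90 | 0.95 |
| Exponential, mean 1 year | 0.94 | 0.98 | 0.93 | 0.97 |
| Exponential, mean 3 years | 0.98 | 0.99 | 0.98 | 0.99 |
| Uniform 0–10 years | 1.00 | 1.00 | 1.00 | 1.00 |
| Uniform 1–2 years | 1.04 | 1.02 | 1.06 | 1.03 |
| 2 years or later | 1.00 | 1.00 | 1.00 | 1.00 |

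**Events and person-time both removed.** The first-event rate ratio was 0.997 to 1.006 in every scenario, which is 1.00 within simulation error. With exact duration matching it is also 1.00, even if only events are deleted.

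**Crude proportions (chi-squared).** There is no person-time denominator, so cutting person-time does not help. The proportion without an event is the mean of exp(−0.2(F − loss)). For DSME uniform over the first year:

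- Attenders: exp(−0.2F) × (e^0.2 − 1)/0.2 = exp(−0.2F) × 1.1070.
- Controls: exp(−0.2F) × (1 + 0.1070 × ln 2) = exp(−0.2F) × 1.0742.
- Difference: 0.0328 × exp(−0.2F) = 2.2 points at 2 years, 1.8 at 3 years and 1.2 at 5 years, with attenders lower.

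**The case against.** The strongest reply is that the text never says person-time in the window is kept. Section 3.1 reads naturally as delayed entry, which would remove events and time together, and the rate ratio is then unbiased. Coding of person-time is also a detail that an article may leave to a fuller document. Both parts stand as far as they go: bias in the rate models is conditional. But delayed entry at diagnosis plus 12 months contradicts the explicit DSME-date baseline in section 3.3 for every first-year attender, so the stated rules need reconciling in any case. It also leaves the crude comparison of proportions with unequal windows.

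A second reply is that DSME timing is unknown. Section 3.3 includes patients irrespective of when they receive it, and early and late timings push in opposite directions. This stands too. Under the formulas above the bias is zero where 1 − d = 0.5/(1 + d), that is d = 0.71 years, and changes sign there.

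A third reply is that the exclusion has a second purpose, allowing time for exposure, so deleting it is a matter of choice. That is fair. Giving controls the attender's DSME date already deals with the attender's wait for exposure, but the 12-month rule can be kept without null bias if it is applied as a common start for events and person-time.

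**Conclusion.** The point holds in conditional form. The entry and exclusion rules conflict for patients educated in their first year, and the ±1 year match can give partners different event time. If events alone are removed, the null rate ratio is about 0.91 (2 years) to 0.97 (5 years) for DSME spread over the first year, about 1.04 to 1.02 for DSME at 1 to 2 years, and 1 for DSME from 2 years on. If person-time is cut too, it is 1. The crude proportions remain unequal by about 1.2 to 2.2 points when DSME falls in the first year. All sizes rest on the assumed constant rate, control durations, follow-up and DSME timing. Cox hazard ratios and mortality were not computed separately.

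Three stronger readings are tempting and not supported.

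- A reader might infer that the rate ratio is certainly biased. The protocol does not say person-time is kept, and section 3.1 may mean that it is not.
- A reader might infer a range of about −13% to +9%. That comes from placing every attender at exactly 3 months (2.25/2.60 = 0.865 over 3 years) or exactly 12 months (3/2.75 = 1.091). Neither date is in the protocol, and spread timings give less.
- A reader might infer that controls can enter after the index date and gain immortal time. Section 3.3 asks for controls of matching age, duration "and sex who are present in the dataset from the same start year or earlier", and matches them at a baseline defined as the DSME date. Late entry is therefore speculative.

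**What to change.** Reconcile sections 3.1, 3.2 and 3.3 around one time zero per matched set. Two versions work:

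- Count events and person-time from the attender's DSME date for all members of the set, without the 12-month exclusion.
- If the 12-month rule is kept, apply it as a common landmark: the later of the DSME date and the latest diagnosis plus 12 months in the set. Start both events and person-time there for every member.

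In either version, require every member to be alive, registered and diagnosed on that date, and use the same start for the chi-squared, count and Cox analyses.

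The cost is wording and programming. The landmark version also loses some early follow-up.

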### Data selection

3.3

To minimise the impact of incorrect information or flawed subject selection the ‘*ever’* cohort will be matched at baseline to patients who have ‘*never’* received DSME (*n* = 584 312). Age,^22^, ^23^ age at diagnosis and diabetes duration^22^, ^24^, ^25^, ^26^ are the most important predictors of one‐year mortality in type 2 diabetes.^27^ Every decade of earlier diabetes diagnosis is associated with 3–4 years of lower life expectancy.^24^

Cohort analysis, systematic review and meta‐analysis have considered the association between diabetes and sex, demonstrating that women generally have a higher risk of coronary heart disease and all‐cause mortality (58%) compared to men and a 13%–17% greater risk of all‐cause mortality.^28^, ^29^ Moreover, the additional likelihood of developing cancer and the higher risk of premature mortality from having diabetes is more pronounced in women.^30^

Patients will therefore be matched at baseline for age ± 5 years, age at diagnosis ±5 years, diabetes duration ±1 year and sex who are present in the dataset from the same start year or earlier.

This study will adopt an intention‐to‐treat analysis, with patients contributing only to the original exposure group in which they have been assigned, irrespective of when they receive DSME. Baseline for the ‘ever’ group and their matched controls will be the date of DSME intervention. Patients will remain exposed until they are censored by death, leave the GP practice, leave a GP practice which contributes to CPRD data or end of the study period (29 March 2021).

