### Statistical methods

3.6

Baseline characteristics of participants will be summarised using descriptive statistics (mean, median, interquartile range and standard deviations as appropriate). We will also summarise total number of hospital admissions and length of stay by age, age at time of diabetes diagnosis, diabetes duration, ethnicity and IMD decile.

The primary cohort is those who have ‘*ever*’ received DSME in each of the 10 years in the study to identify hospital admissions and cause of death during follow‐up. We will additionally have a matched diabetes cohort who have ‘*never’* received DSME to provide comparison (rate ratios).

An initial crude analysis will compare the proportion of hospitalisations and deaths between *ever* and *never* DSME groups. Chi‐squared tests will be used to compare these proportions. Similar tests will be used for subgroup analysis and alternative outcomes (cause‐specific hospitalisations and mortality).

Number of hospital admissions will be calculated to estimate relative risk of admissions and mortality by all‐cause and cause‐specific using a mixed Poisson model. Should the data be over dispersed a negative binomial mixed model will be adopted.

A Cox proportional‐hazards model will be used to measure time to event for first hospital admissions and mortality with the proportional hazards assumption checked using Kaplan—Meier curve plots and Schoenfeld residuals tests. If the proportional hazards assumption does not hold, then alternatives such as restricted mean survival times models will be used.

Baseline covariates will be reported among the ‘ever’ and ‘never’ groups, and a statistical test will be applied to see whether these differ significantly. These will be examined in multivariate models. We will address potential issues with confounding by indication firstly within the study design in which individuals in the ever group will be matched at baseline for age, sex, diabetes duration and age at diagnosis to individuals in the never group. All models will be adjusted a priori for CCI, IMD, HbA1c, BMI, smoking status, lipid level and SBP during multivariate analysis.

Statistical analysis will be conducted using R version 4.4.1. Alpha level will be set at 5% for statistical significance.

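### Controls are tied to the attender's start year, not to observation on the index date, so some can be given a baseline before they entered the data

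*Protocol article*

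**What the plan says.** Section 3.3 (Data selection) matches controls on sex, age, age at diagnosis and diabetes duration. It adds one condition on calendar time: controls are those "who are present in the dataset from the same start year or earlier". The term start year is not defined; it could mean the year of dataset entry or the year of DSME.

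The same section fixes time zero to the day. Baseline for the 'ever' "group and their matched controls will be the date of DSME intervention". It then lists how follow-up ends (death, leaving the practice, the practice leaving CPRD, 29 March 2021). It gives no rule for when observation must have begun.

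On the exposed side, section 3.2 (Sample) defines the group by a code: "The primary cohort is those who have a READ code confirming they have" ever received DSME. Section 3.3 assigns patients to groups "irrespective of when they receive DSME". The study dates in section 3.1 apply to patients "registered to an English GP practice between 29 March 2011 and 29 March 2021", not to the DSME code. Section 3.6 describes the primary cohort as those who have ever "received DSME in each of the 10 years in the study to identify hospital admissions". That could mean DSME within the ten study years, or 'ever' status assessed in each year.

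The one stated guard against immortal time, in section 3.2, drops admissions and deaths in the first 12 months after diagnosis in both groups.

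**The concern.** Eligibility is set to the year and time zero to the day. Take an attender who joins in February 2013 and attends DSME in April 2013. A control who first appears in November 2013 meets the start-year rule and receives an April 2013 baseline, seven months before entry. That control had to be alive in November to be in the data at all, so no death can fall in those seven months. Admissions in that time may be unobserved, depending on whether hospital records from before registration are used, which is not stated.

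If that time counts as follow-up, the control rate is too low and the ratio moves against DSME. The 12-month exclusion does not help, because it is anchored to diagnosis: a patient diagnosed years earlier who newly joins a contributing practice is untouched by it. Mortality and time to first admission are core outcomes, and the article itself names immortal time bias as something it means to handle.

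A similar gap can arise for attenders. If a DSME code predates the attender's own observation, the attender had to survive to be included.

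**Working it through.** The article gives no figure on this point, so there is none to reproduce. It does not report how many controls share a start year, how large the gaps are, or the mean follow-up. The numbers below are illustrations under stated assumptions.

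**1. Share of same-start-year controls who enter late, and by how much.** Assume dates are uniform within a year, with time in years.

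- *Start year means dataset entry, and the attender's entry and DSME both fall in that year.* Given entry before DSME, the DSME date d has density 2d. P(control enters after d) = ∫2d(1−d)dd = 1/3. Expected time lost per same-start-year control = ∫2d·(1−d)²/2 dd = 1/12 = 0.083 years. Mean gap among late entrants = (1/12)/(1/3) = 0.25 years, or 3 months.
- *Start year means the year of DSME.* P(control enters after d) = 1/2. Expected time lost = 1/6 = 0.167 years. Mean gap = (1/6)/(1/2) = 1/3 year, or 4 months. A simulation of one million date pairs gave 0.49983 and 4.0003 months.

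On either reading a single gap can reach just under 12 months.

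**2. Effect on the first-year ratio when DSME has no effect.** Let s be the share of controls with the same start year and g the expected time lost. Controls are credited with 1 year but are truly at risk for 1 − s·g, so the apparent ratio is 1/(1 − s·g). The range s = 5–30% is an assumption.

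| s | g = 0.083 | g = 0.167 |
|---|---|---|
| 5% | 1.004 | 1.008 |
| 30% | 1.026 | 1.053 |

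**3. Over longer follow-up.** With mean follow-up of 4 years (assumed), the ratio is 1/(1 − s·g/4).

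- Lowest: 0.05 × 0.083/4 = 0.001, giving 1.001.
- Highest: 0.30 × 0.167/4 = 0.0125, giving 1.013.

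**4. Sensitivity to the assumptions.** Let f be the share of controls with a gap, g the length of that gap and T the mean observed follow-up; the ratio is (T + f·g)/T. For f = 5–20%, g = 4–12 months and T = 3–5 years, it runs from (5 + 0.05 × 0.333)/5 = 1.003 to (3 + 0.20 × 1)/3 = 1.067.

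**5. Attender side.** If the gap lay in attenders only, the ratio would be T/(T + f·g). For gaps of 1–3 years with the same f and T, it runs from 5/(5 + 0.05 × 1) = 0.990 to 3/(3 + 0.20 × 3) = 0.833, in favour of DSME. This shows the possible direction only: where the control has the same gap and the same need to survive to entry, the effect is at least partly shared.

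**6. After the fix.** If everyone is under observation at time zero, or enters the risk set only when observation starts, g = 0 and the ratio is 1.00.

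**The case against.** The best defence is that this is a condensed article. Filters for being alive and registered are often left to the full approved protocol, which is not shown, and they may well be applied. That would settle the matter if the article were silent. It is not: it states a calendar condition for controls, and that condition is too coarse for the time zero it is paired with.

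A second defence is the complete-case primary analysis in section 3.7. A late entrant with no baseline covariates would drop out of the adjusted models. This has some force, but data count as missing only when there is no record within 12 months of baseline, and no direction is given. A measurement taken after baseline could keep the late entrant in, and the crude comparisons are unaffected in any case.

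Several stronger readings are tempting and are not supported:

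- *Controls may be undiagnosed at baseline.* Section 3.1 admits patients "12 months from the first use of a clinically recorded diagnosis of type 2 diabetes", and section 3.4 measures duration from the first diagnosis code. A control not yet diagnosed would need a negative duration, which nothing in the text allows.
- *'Ever' plainly has no date limit.* Section 3.6 can be read as confining DSME to the study years, and the phrase "irrespective of when they receive DSME" sits in a sentence about group assignment. The text is unclear rather than open-ended. Even the narrower reading does not exclude a code dated before the patient's own registration.
- *Attenders educated before 2011 bias the ratio in a known direction.* Attender and control share the index date, so a shared gap has no clear direction.
- *Controls who left or died before the index date add event-free time.* They contribute no follow-up, so they add none.
- *No event of any kind could occur in the gap.* That is strict only for death.

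**Conclusion.** The point holds in a limited form. As written, section 3.3 admits controls who enter the data after their own baseline, and nothing else in the article closes that gap. Taken alone it biases the ratio slightly against DSME: about 1.004–1.05 in the first year and about 1.001–1.013 over 4 years when the true ratio is 1. These figures rest on uniform dates, an assumed 5–30% share of same-start-year controls and an assumed 4 years of follow-up. If start year means dataset entry, they are upper values, because a gap then arises only where the attender's entry and DSME fall in the same year.

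The dating of the DSME code is a separate ambiguity that could place an attender's baseline before observation. A reader might infer that the study is seriously biased, or biased in a known direction overall. The document supports neither: the two routes can pull in opposite directions, and it gives nothing from which to size them. The change is worth making because it is cheap and serves the article's own aim of handling immortal time.

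**What to change.** Replace the start-year condition in section 3.3 with: on the attender's index date the control must be alive, registered in a contributing practice and already meeting the cohort entry criteria.

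Define the index date as the first DSME code, and require it to fall between 29 March 2011 and 29 March 2021 while the attender is registered. Apply the cohort entry criteria to attender and control alike. If attenders with codes outside that period are to be kept, let them and their controls enter the risk set only from the start of observation (delayed entry).

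The cost is one matching filter and one date restriction. Some attenders whose first code falls outside the period would be lost; the article does not allow that number to be estimated. With 584 312 potential controls, match rates should change little.
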